### Study design

Patients will be randomly assigned to discharge from acute care with the TOC tool (intervention group) *versus* usual care (control group). The intervention will consist of patient’s acute-care stay summaries being generated with the use of the computer-enabled communication tool. The tool provides a standardized template for communicating all relevant clinical information on patients who are leaving hospital, is immediately available at time of leaving and is accessible through the web by community-based providers (family physicians, specialists, home care nurses, and community pharmacists). Figure
1, Figure
2, Figure
3 show screen shots taken from various points in the TOC tool. This is in contrast to current summaries that the control group will receive under usual care (control group). Usual care involves using the traditional model of TOC communication with dictated/transcribed summaries. This usual care typically involves paper-based handwritten summaries with subsequent provision of a dictated summary produced some time after the patient leaves hospital, with unpredictable success and timing of delivery and with unstructured and sometimes haphazard content.

**Figure 1 F1:**
[figure not shown]
The introduction page for a test patient from the seamless transfer-of-care tool.

**Figure 2 F2:**
[figure not shown]
The medication details off of a test patient from the seamless transfer-of-care tool.

**Figure 3 F3:**
[figure not shown]
Existing health issues off of a test patient from the seamless transfer-of-care tool.

Upon admission to the MTU, the research team will approach the patient for consent and will collect baseline data including socio-demographic information, co-morbidities (using the Charlson co-morbidity measurement method
[21]), and current health status using the Health Utilities Index (HUI)
[22,23]. A chart review will be conducted on each patient. This information will be collected on a secure, web-based program that was developed by the University of Calgary’s new Clinical Trial Research Unit (CRU). The CRU has also generated a web-based method for random allocation of patients to intervention *versus* control. Randomization will be requested from the investigators, and will be entirely concealed from the researchers. Randomization will be performed within 48 hours of patients leaving hospital rather than at the time of them leaving due to the nature of the MTU in which, decisions about when patients can leave often occur without much notice and residents often do not have time to complete a summary immediately given competing clinical activities. To ensure that patients will be leaving the hospital with either a copy of the completed summary produced by the TOC tool or, conversely, a hand written note for the control group, the summaries will be started by providers some time prior to the patient leaving. Figure
4 provides a summary of this process.

**Figure 4 F4:**
[figure not shown]
Flowchart of the protocol for the seamless transfer-of-care study.

### Study measures

#### Baseline measures

**Patient sociodemographic characteristics** At the first study visit (baseline assessment) the patients will be presented with a brief sociodemographic questionnaire. Items included are age, sex, level of education, employment status, and admission diagnosis.

#### Chart review

Information about the patients’ admission to the MTU, comorbidities, medication changes, alcohol and substance abuse, and living arrangements will be collected from patients’ hospital charts prior to their discharge from hospital.

### Outcome measures

The primary outcome of interest for the clinical trial is the composite, at 3 months, of death or readmission to any Alberta acute-care hospital. Secondary outcomes of interest are the occurrence of post-discharge adverse events and adverse drug events at 1 month post discharge. Patient health status, meanwhile, will be assessed at baseline, 1 and 3 months using the Health Utilities Index
[22,23].

The elements of our composite primary outcome (i.e., death or readmission) are identified for study because these are recognized to be major events that we are ultimately trying to prevent through safer health care. The 3 month time frame is felt to be most relevant, because it is short enough to potentially relate to discharge communications, but also long enough after discharge to permit some events to accrue. The primary outcomes of interest will be assessed through existing linkages to hospitalization data from the Alberta Health Services Health Outcomes Group (for readmission to acute care hospitals), and to the Alberta Vital Statistics for post-discharge mortality. Such an approach to post-discharge outcome ascertainment avoids the shortcoming of unreliable patient self-report on readmission, and the potential challenges associated with determining vital status of patients that we are unable to reach by telephone.

The outcomes of post-discharge adverse events and adverse drug events will be determined using the method described by Forster and colleagues
[24,25]. At 1 month post discharge, a trained investigator, blinded to patient group assignments, will administer a telephone survey using a survey tool that takes approximately 15 minutes to complete to determine the post-hospital course for all consenting patients. This will allow us to determine readmission/physician visits/emergency department visits, and whether an adverse event or adverse drug event occurred. Two Royal College certified internists or College-certified family physicians, also blinded to patients’ group assignments, will independently rate the type, severity, preventability and ameliorability of all possible adverse events. Adverse events will be classified into the following types: 1. adverse drug events; 2. procedure-related injury; 3. nosocomial infection, 4. care-related fall, 5. therapeutic error, 6. diagnostic error or 7. other types. Further information on this validated multi-step method is available elsewhere
[24,25].

#### Health utilities index

Patient health status and health-related quality of life (HRQOL) will be measured using the Health Utilities Index Mark 3 (HUI3)
[22,23]. HUI3 assesses a full range of health among diverse groups of patients and reflects co-morbidities, and has been widely used in every major Statistics Canada population health survey in Canada since 1990
[23]. Additionally, the HUI3 can be converted to a utility score; the required input to calculate the cost per QALY gained. During the 1 and 3 months post-hospital stay, a trained investigator, blinded to patient group assignments, will administer a telephone version that takes approximately 15 minutes to complete.

#### Economic evaluation

The economic evaluation will have two primary outcomes: the cost per life and the cost per hospital readmission avoided using the TOC communication tool compared to traditional dictation. A secondary outcome will be the cost per QALY gained using the web-based TOC communication tool compared to traditional dictation. All outcomes (clinical events and utility scores) will be assessed through the clinical arm of the RCT. The cost of the TOC communication tool will be calculated from corporate financial data including the cost of development, implementation, integration and training. The cost of dictation (for type-written dictated discharge summaries the usual mode of discharge summary creation in the absence of this discharge tool) will be estimated based on physician time, transcription costs, and dissemination costs. Costs of on-going care will be estimated from administrative data including ER visits, physician visits and hospitalization. Total costs of care and outcome events will be calculated for each arm of the trial. For each objective, the cost difference between arms will be divided by the benefit difference to result in cost to benefit ratio.

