### Sample size calculation and anticipated patient enrollment

As previously mentioned, a recent pilot done by the W21C team demonstrated that patients discharged from the MTU had a 23% probability of readmission to Calgary hospitals within 3 months (51 out of 219 discharged patients assessed in a pilot chart review). From this, we estimate an absolute event rate of 25% in the control group for the composite of death or readmission, and have designed our study to detect an approximately 25% relative reduction (i.e., a 6.25% absolute reduction) in the readmission rate in the intervention group. Therefore, using p_1_=0.25, and p_2_=0.1875, with alpha=0.05 and beta=0.80 in our two-tailed sample size calculation, we will require 686 patients per group. Our research plan is to enroll 700 patients per group, allowing for a safety margin for attrition. Each of the three teams usually processes an average of 2 to 4 discharges per day. As such, we anticipate that we will complete enrollment of 1400 subjects within an 18 month period and full assessment of outcomes and follow-up surveys in a 2 year period. For the secondary endpoints of post-hospital adverse events and adverse drug events, we will have adequate statistical power given that these adverse events are known to occur frequently, in approximately one quarter of patients discharged from acute-care hospitals
[1,2]. The sample size is appropriate to assess patient health status measured by HUI3 to compare two independent means for a parallel trial design, 697 patients in each group are needed to detect a clinically important difference (CID) in HUI3 overall score of 0.03 (SD=0.20).

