### Data analysis

The baseline characteristics (age, sex, principal diagnosis categories, and comorbididy conditions) of intervention and control subjects will be recorded and compared between groups using Chi-square tests or Fisher Exact tests where appropriate. We will also use t-tests for comparison of continuous variables. The same statistical tests will be used to compare outcomes between the two groups. Chi-square and Fisher exact tests will be used to compare the frequency of dichotomous outcomes (i.e., death or readmission, adverse events, adverse drug events). For the subset of patients who are readmitted in the two groups, we will use t-tests to compare the time-to-readmission of patients and patient health status (HUI3 overall scores) in the intervention *versus* control groups. A Kaplan-Meier analysis with log-rank test will be used to perform a time-to-event analysis in all subjects. For the economic evaluation, total costs of care and outcome events will be calculated for each arm of the trial. For each outcome, the cost difference between arms will be divided by the benefit difference to result in cost to benefit ratio.

The analysis will be performed by intention-to-treat. Patients will be analyzed in the group to which they were randomized, even if the summary of their hospital stay is generated using a communication method that differs from their group assignment. CONSORT reporting guidelines (
http://www.consort-statement.org) will be used to diligently track and report treatment crossovers and losses to follow-up through a progressive flow-chart. We will work diligently during the course of the study to limit the frequency of such occurrences. This will be achieved by a system of clear labeling of patient charts immediately after random allocation so that the care team will be aware of the assigned summary of care communication method. Research associates affiliated with the study will also be present among the clinical care team daily to reinforce the issue of compliance to patient assignments.

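### Cost per life is made a primary economic ratio, but at 700 patients per arm its divisor, the difference in deaths, cannot be told from zero

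*Protocol article*

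**What the plan says.** The Economic evaluation section of the protocol article names "two primary outcomes: the cost per life and the cost per hospital readmission avoided", and adds: "A secondary outcome will be the cost per QALY gained". The Abstract makes clear that the first of these means cost per life saved.

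The estimator is stated twice. The Economic evaluation section says that "the cost difference between arms will be divided by the benefit difference to result in cost to benefit ratio", and the Data analysis section repeats it: "For each outcome, the cost difference between arms will be divided by the benefit difference to result in cost to benefit ratio". Both places also say that total costs and outcome events will be worked out for each arm.

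The sample size section sizes the trial on the composite of death or readmission, "using p_1_=0.25, and p_2_=0.1875, with alpha=0.05 and beta=0.80 in our two-tailed sample size calculation", and describes the target as an "approximately 25% relative reduction (i.e., a 6.25% absolute reduction) in the readmission rate in the intervention group". The result is 686 per group, with 700 to be enrolled. The article gives no death rate and no power for death alone. The Data analysis section lists the composite, not death alone, among the dichotomous comparisons. The Discussion nonetheless counts mortality among the outcomes the trial has power to settle.

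**The concern.** Under the stated rule, the divisor for cost per life is the between-arm difference in deaths over 3 months. Death is only one part of the composite on which the trial is sized. If that difference is small relative to its standard error, three things follow.

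- The ratio swings over a very wide range, because it is unbounded as the divisor approaches zero.
- The divisor can take the wrong sign by chance.
- If deaths tie, the ratio does not exist.

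The sign of a ratio is also ambiguous. A negative value arises when the tool is cheaper and saves lives, and equally when it is dearer and loses them. A positive value arises when it is dearer and better, and equally when it is cheaper and worse.

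At stake is one of the two results designated primary for the cost-effectiveness objective, in an article that offers its findings to other health systems as evidence on value for money.

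**Working it through.** **1. The plan's own figure.** Inputs from the sample size section are p1 = 0.25, p2 = 0.1875, two-sided alpha 0.05 and power 0.80. The article writes the last as beta, but the stated n reproduces only if it is power. With pooled variance and no continuity correction, mean p = 0.21875:

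n = [1.960 × √(2 × 0.21875 × 0.78125) + 0.8416 × √(0.25 × 0.75 + 0.1875 × 0.8125)]² / 0.0625² = (1.1459 + 0.4906)² / 0.003906 = 685.6, so 686.

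This matches. The sizing is sound for the composite, and for the composite only.

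**2. The missing input.** Control mortality is not given. The only hint is the gap between the assumed composite rate (25%) and the pilot readmission rate (51/219 = 23.3%), about 2 points. That gap approximates only deaths without readmission. Part of it may also reflect the move from Calgary hospitals in the pilot to all Alberta hospitals in the trial. So 2% is an assumption, and 1% to 10% is shown.

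**3. The death difference at 700 per arm.** Assume the 25% relative reduction also applies to death, so p2 = 0.75 × p1. Then d = p1 − p2, SE = √[(p1(1−p1) + p2(1−p2))/700], the 95% range is d ± 1.96 × SE, and P(wrong sign) = Φ(−d/SE). At 2%: SE = √[(0.0196 + 0.014775)/700] = 0.0070, d/SE = 0.005/0.0070 = 0.71, Φ(−0.71) = 0.24.

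| Control mortality (assumed) | Expected deaths | d (points) | 95% range (points) | P(wrong sign) | Power for death | n per arm for 80% power |
|---|---|---|---|---|---|---|
| 1% | 7.0 v 5.2 | 0.25 | −0.73 to 1.23 | 0.31 | 0.07 | 21,784 |
| 2% | 14.0 v 10.5 | 0.50 | −0.87 to 1.87 | 0.24 | 0.11 | 10,795 |
| 5% | 35.0 v 26.3 | 1.25 | −0.89 to 3.39 | 0.13 | 0.21 | 4,202 |
| 10% | 70.0 v 52.5 | 2.50 | −0.46 to 5.46 | 0.05 | 0.38 | 2,005 |

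Every range includes zero.

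**4. Check by simulation.** In 400,000 binomial draws at 2% v 1.5%, the difference was negative in 20.7% and exactly zero in 6.4%. The normal figure of 24% splits the ties: 20.7 + 6.4/2 = 23.9. So the chance of a strictly wrong sign is about 21%, plus about 6% in which the ratio is undefined.

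**5. Effect on the ratio.** For illustration only, assume a cost difference of 100 per patient and 2% mortality. The ratio is 100/0.0050 = 20,000 per life at the true effect, 100/0.0187 = about 5,300 at one end of the 95% range, and 100/(−0.0087) = about −11,500 at the other. Between the last two it is unbounded.

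**6. The other divisors.**

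- Readmission, 23.3% v 17.5%: d = 5.8 points, SE 2.15, d/SE = 2.71, 95% range 1.6 to 10.0, P(wrong sign) = 0.003. With a 12.5% relative reduction P(wrong sign) is about 0.09, with 10% about 0.15, and with no effect about one half.
- HUI3 at the stated difference of 0.03 with SD 0.20: SE = 0.20 × √(2/700) = 0.0107, d/SE = 2.81, P(wrong sign) = 0.003. The divisor in QALYs is small in absolute terms, at most 0.03 × 0.25 year = 0.0075, but it is not unstable at the design effect.

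**The case against.** The strongest reply has four parts.

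First, cost difference over effect difference is the usual cost-effectiveness estimator, and a journal article normally leaves intervals, resampling and sign handling to a fuller plan. This stands. A reader might infer that the ratios will be published with no statement of uncertainty, but nothing in the article says so, and silence here is not a finding.

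Second, a reader might infer that the whole economic result rests on a near-zero divisor and is uninterpretable. The article's own assumptions contradict that: the readmission and HUI3 divisors are about 2.7 and 2.8 standard errors from zero. They become fragile only if the true effect is much smaller than planned.

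Third, costs and events are to be totalled by arm, so a reader shown those totals could tell cheaper-and-better from dearer-and-worse and could see how few deaths separate the arms. This softens the sign ambiguity. It does not stabilise the ratio or define it when deaths tie.

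Fourth, the death figures rest on an assumed mortality and on carrying to death a 25% reduction stated for the composite and for readmission. That is so, and the size of the problem depends on both. A weaker effect on death makes matters worse: with a 10% relative reduction the wrong-sign chance is 39% at 2% mortality and 26% at 10%. A stronger effect would help.

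What the reply does not reach is the endpoint choice. A fuller plan could add intervals, but it would still inherit cost per life as a primary ratio.

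**Conclusion.** The point holds for cost per life. The article fixes it as a primary economic outcome and fixes its definition, in a trial sized only on the composite. With 700 per arm and a 25% relative reduction in death, the 95% range for the divisor includes zero at every assumed control mortality from 1% to 10%. The wrong-sign chance falls from about 31% to about 5% across that range, and power for death alone rises from 7% to 38%. Followed as written, the rule can give a primary result that is unstable, ambiguous in sign and occasionally undefined.

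The conclusion rests on two assumptions, the mortality range and the carry-over of the 25% reduction to death. It does not extend to cost per readmission avoided or to cost per QALY at the design effect, and the ratio estimator is not wrong in itself. Because cost-effectiveness is a secondary objective with three ratios, the overall economic conclusion need not turn on deaths. This is a change that should be made, not a fault in the trial's main analysis.

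**What to change.** - Report cost per life as descriptive only, and keep cost per readmission avoided as the primary economic result.
- For every economic outcome, report incremental cost and incremental effect separately, with 95% intervals from a joint patient-level bootstrap that resamples each patient's cost and outcome together.
- Base the conclusion on incremental net benefit (willingness-to-pay × effect difference − cost difference) over a stated range of willingness-to-pay. This stays defined when the effect difference is zero or negative.
- Show the ratio only where the effect difference is clearly positive.

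The change needs no extra patients or visits. It costs some analysis programming and the loss of a headline cost-per-life figure. It assumes that the administrative data on emergency visits, physician visits and hospital stays can be held per trial patient. The article describes linkage for readmission and death but does not say this outright for every cost item. The cost of the tool, taken from corporate accounts, would enter as a fixed amount per intervention patient.

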### Sample size calculation and anticipated patient enrollment

As previously mentioned, a recent pilot done by the W21C team demonstrated that patients discharged from the MTU had a 23% probability of readmission to Calgary hospitals within 3 months (51 out of 219 discharged patients assessed in a pilot chart review). From this, we estimate an absolute event rate of 25% in the control group for the composite of death or readmission, and have designed our study to detect an approximately 25% relative reduction (i.e., a 6.25% absolute reduction) in the readmission rate in the intervention group. Therefore, using p_1_=0.25, and p_2_=0.1875, with alpha=0.05 and beta=0.80 in our two-tailed sample size calculation, we will require 686 patients per group. Our research plan is to enroll 700 patients per group, allowing for a safety margin for attrition. Each of the three teams usually processes an average of 2 to 4 discharges per day. As such, we anticipate that we will complete enrollment of 1400 subjects within an 18 month period and full assessment of outcomes and follow-up surveys in a 2 year period. For the secondary endpoints of post-hospital adverse events and adverse drug events, we will have adequate statistical power given that these adverse events are known to occur frequently, in approximately one quarter of patients discharged from acute-care hospitals
[1,2]. The sample size is appropriate to assess patient health status measured by HUI3 to compare two independent means for a parallel trial design, 697 patients in each group are needed to detect a clinically important difference (CID) in HUI3 overall score of 0.03 (SD=0.20).

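### The HUI3 sample size counts enrolled patients as evaluable: 697 of 700 per group must give telephone scores, so calling the size appropriate assumes almost complete follow-up

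*Protocol article*

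**What the plan says.** The section on sample size and enrollment first sizes the primary outcome: event rates of 0.25 and 0.1875, "with alpha=0.05 and beta=0.80 in our two-tailed sample size calculation", giving "we will require 686 patients per group". (The 0.80 is printed as beta but is evidently the power.) It continues: "Our research plan is to enroll 700 patients per group, allowing for a safety margin for attrition". At the end of the section it turns to HUI3: "The sample size is appropriate to assess patient health status measured by HUI3 to compare two independent means for a parallel trial design", because "697 patients in each group are needed to detect a clinically important difference (CID) in HUI3 overall score of 0.03 (SD=0.20"). No HUI3 loss rate and no HUI3-specific inflation are given.

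The Health utilities index section says that at 1 and 3 months a blinded investigator "will administer a telephone version that takes approximately 15 minutes to complete". The Outcome measures section takes death and readmission from provincial hospitalization and vital statistics data. One reason it gives is the possible difficulty of establishing vital status in patients who cannot be reached by telephone. HUI3 is also measured at baseline. The Data analysis section names t-tests for HUI3, with no baseline adjustment, in a sentence that opens by restricting to readmitted patients.

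**The concern.** A required number of 697 and an enrolment of 700 look comfortable side by side, but they count different things. The 697 is a number of patients with a HUI3 score at follow-up, and the 700 is a number randomized. The gap between them has to absorb every patient who does not complete the telephone interview and every death not given a utility value.

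The attrition margin does not fill that gap. It is stated straight after the primary requirement of 686, and it protects an outcome obtained by linkage, where loss should be small. Linkage cannot supply a HUI3 score. The outcome most exposed to loss therefore has the smaller margin.

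What is at stake is how the HUI3 comparison is described. The article presents it as sized for a clinically important difference and promises evidence on health status in its Discussion. A reader would credit the comparison with the conventional 80% power, which it has only if almost nobody is lost.

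**Working it through.** **Inputs from the protocol article.** HUI3 difference 0.03 and SD 0.20 (standardized difference 0.03/0.20 = 0.15); 697 per group stated as needed; 700 per group planned; 686 per group for the primary outcome. Two-sided alpha 0.05 and 80% power are stated for the primary outcome only and are taken here to carry over to HUI3.

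**Step 1. Reproduce 697.** n per group = 2 × (z for alpha + z for power)² × SD² / difference².
- Rounded z values: 2 × (1.96 + 0.84)² × 0.04 / 0.0009 = 696.9, i.e. 697.
- Unrounded: 2 × (1.95996 + 0.84162)² × 0.04 / 0.0009 = 697.7, i.e. 698.
- Based on the t distribution: 698.6, i.e. 699.

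One-sided testing would give 550, and 90% power would give 934. So 697 is the two-sided 5%, 80% power figure with nothing added for loss.

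**Step 2. The margins.**
- HUI3: 700 − 697 = 3 per group; 3/700 = 0.43%.
- Primary outcome: 700 − 686 = 14 per group; 14/700 = 2.0%. The 686 also reproduces from 0.25 against 0.1875.

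**Step 3. Power for 0.03 with 700 enrolled per group.** The article gives no completion rate, so the rates below are assumptions. Power is for the unadjusted two-sample t-test (noncentral t). The detectable difference at 80% power is (1.95996 + 0.84162) × 0.20 × √(2/n).

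| Assumed completion | n per group | Power for 0.03 | Detectable difference |
|---|---|---|---|
| 100% | 700 | 80.1% | 0.0300 |
| 95% | 665 | 78.0% | 0.0307 |
| 90% | 630 | 75.8% | 0.0316 |
| 80% | 560 | 70.8% | 0.0335 |
| 70% | 490 | 65.0% | 0.0358 |

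Keeping 697 evaluable by enrolment alone would take 697/0.90 = 775 per group at 90% completion, or 697/0.80 = 872 at 80%.

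**Step 4. What baseline adjustment could recover.** With correlation r between baseline and follow-up HUI3, the residual SD is 0.20 × √(1 − r²). The correlation is also an assumption, since the article gives none.

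| Assumed completion | r = 0.3 | r = 0.4 | r = 0.5 |
|---|---|---|---|
| 90% | 79.6% | 82.7% | 86.7% |
| 80% | 74.8% | 78.1% | 82.5% |
| 70% | 69.1% | 72.6% | 77.3% |

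**Step 5. The population of the HUI3 t-test.** Read literally, the Data analysis sentence compares HUI3 among readmitted patients only. As a rough guide, applying the design rates for the composite gives 700 × 0.25 = 175 and 700 × 0.1875 = 131 patients. The standard error is 0.20 × √(1/175 + 1/131) = 0.023, and power for 0.03 is about 25%. The 697 clearly assumes all patients, and the same section says more generally that the same tests will be used to compare outcomes between the two groups. The two statements need to be reconciled.

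**The case against.** The strongest reply is that nothing has been miscalculated and that the shortfall is hypothetical. The first half stands: 697 reproduces, and a reader who infers an arithmetic error would be wrong. The second half stands in part. At 700 evaluable per group the power is 80.1%, the decline is gradual, and at 95% completion it costs only about two percentage points. Every figure below 80.1% depends on a completion rate the article does not give.

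The exclusion criteria also help. Patients who cannot give contact information, are incoherent, cannot communicate with the team in English, live outside Alberta or are going to hospice are not enrolled. That weakens any presumption of 20% to 30% loss. It does not bring loss under 0.43%, which is passed at the fourth patient per group.

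Deaths need not be lost: they could be scored, for example as zero utility, and that rule may sit in an analysis plan that is not shown. Telephone non-contact alone would still use up a margin of 3. The article mentions unreachable patients as a possible difficulty. That falls short of predicting a rate, so it supports only the statement that some loss is foreseen.

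A reader might also infer that the cost-per-QALY result is undermined. The article does not support that: the ratio is a cost difference divided by a benefit difference and does not rest on the power of a HUI3 t-test. Nor does the point touch the primary outcome, which has its own calculation and its own margin.

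Finally, whether to adjust for baseline is often left to an analysis plan. That is fair, and the absence of adjustment is not the fault here. Adjustment is offered as a remedy, and its benefit depends on the correlation.

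**Conclusion.** The point holds in a limited, conditional form. The protocol article treats enrolled patients as evaluable for HUI3, so its claim that the size is appropriate is true only with essentially complete telephone follow-up: a loss of no more than 3 per group, or 0.4%. Under assumed completion of 95%, 90% and 80%, unadjusted power for a difference of 0.03 is about 78%, 76% and 71%.

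This rests on three assumptions: that the HUI3 calculation used 80% power (inferred because it reproduces 697), that the comparison is meant for all patients, and the completion rates themselves. The stronger statement, that the trial cannot detect 0.03, does not follow: the size of the shortfall is unknown, and it is a few points of power unless loss is substantial. HUI3 is not the primary outcome, and it is listed apart from the named secondary outcomes of adverse events and adverse drug events. The point is minor.

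**What to change.** 1. In the sample size section, replace the statement that the size is appropriate for HUI3 with the power for 0.03 at an explicit assumed completion rate, for example about 76% at 90% or 71% at 80% without adjustment. Say that the attrition margin refers to the primary outcome.
2. Make the HUI3 comparison a model adjusted for the baseline HUI3 already collected, in all randomized patients with follow-up. State the assumed baseline-to-follow-up correlation with the resulting power: at 80% completion, about 75% at r = 0.3, 78% at r = 0.4 and 82.5% at r = 0.5. The adjustment offsets some or all of the loss depending on that value, so full recovery should not be promised.
3. Reword the Data analysis sentence so that HUI3 is not tied to the readmitted subset, or say plainly that a subset comparison is a separate and much smaller analysis.
4. State whether deaths are scored or treated as missing for HUI3, or point to where that is specified.

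The cost is one slightly less favourable figure and a few lines of wording. No extra patients or data are needed, and the primary analysis is unchanged.
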